### Participant timeline {13}

The total duration of participation in the study will be 30 days. The forecast study duration is 36 months from first to last patient recruitment (Table 1).

**Table 1 Tab1:** Template of recommended content for the schedule of enrolment, interventions and assessments

	Visit				
	Information	Enrolment	Allocation, visit 0	Post-allocation, visits 1–7	Close-out
Timepoint	Day 0	Day 0	Day 0	Days 1–7	Day 30
Location	Hospital	Hospital	Hospital	Hospital	Hospital
Next of kin information	X*	X*	X		
Signed informed consent		X*			
Plasma **β**HCG assay		X(*)			
Eligibility criteria check	X*	X*	X*		
Randomization			X*		
Study drug administration			X*^d^	X*^d^	
Clinical examination^a^		X	X	X	
Diagnostic tests^b^		X	X	X	
Blood assay^c^			X*	X*	
Adverse effect recording		X*	X*	X*	X*
Concomitant medications		X	X	X	X

*βHCG* beta human chorionic gonadotropin, *X* diagnostic test performed on a daily basis according to the standard of care in participating centres, *X** diagnostic tests performed for the purpose of the TRAUMADORNASE study

^a^Clinical examination includes physical examination (auscultation of the chest, central body temperature, positive end-expiratory pressure and inspired oxygen fraction levels) and recording of Utstein criteria [49]

^b^Diagnostic tests include arterial blood gases, chest X-ray, leukocyte and platelet counts, creatinine, blood urea nitrogen, bilirubin and quantitative lung bacteriologic samplings (bronchoalveolar lavage fluid or protected specimen brush) in the case of suspected lung infection

^c^Blood withdrawal: 6 ml of blood on day 0, day 3 and day 5

^d^Study treatment will be given on day 0 and day 1

### Sample size {14}

The sample size was determined to be 250 subjects per arm (i.e. 500 subjects in total). Dornase alfa is expected to reduce the incidence of moderate-to-severe hypoxaemia from 0.45 to 0.30. Considering a reasonable standard deviation of 0.03, and using Bayesian techniques [52], 200 subjects per arm were estimated to show a difference of more than 0.12 (instead of the expected 0.15). Assuming 25% loss to follow-up, this number was increased to 250 subjects per arm, although these subjects will not be replaced.

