The aim of this study is to show that the frequency of moderate-to-severe hypoxaemia is lower in the dornase alpha group than in the placebo group. The main variable is then dichotomous “moderate-to-severe hypoxaemia yes/no”, modelled in a logistic mixed regression. We will assume that this variable is Bernoulli distributed with parameter π. The logit of this parameter (linear predictor) is additively written as:
$$ \mathrm{logit}\left({\pi}_i\right)={\alpha}_0+{\alpha}_1I\left({g}_i=1\right)+{\beta}_i, $$

where:
*α*_0_ is a grand mean, with mean 0 normal prior (the variance in this normal is 6, corresponding to a low informative prior)*I*(*g*_*i*_ = 1) is a dummy covariate coded for the group of subject *i* (1 for the dornase alpha group and 0 for the placebo group) — the prior on the parameter of this covariate is the same normal as that for the grand mean*β*_*i*_ is a (random) subject effect, on which is assumed a normal prior with mean 0 and low variance (e.g. 10)

Because the linear predictor is on the logit scale, the probability for moderate-to-severe hypoxaemia will be obtained by monitoring the back-transformation of the logit.

This regression model without covariates except group will be completed for taking into account potential confounding variables. In the model, the entire set of these variables will be added and, secondly, selected using stochastic search variable selection (SSVS) [53]. In such a model, the prior distribution on each parameter is a mixture of two mean 0 normal distributions, one with low variance and the other with high variance: if the posterior weight on this second normal is strongly around 0, then the prior on the parameter is essentially driven by a normal distribution whose mean is centred on 0; this is the clue for a “non-significant” parameter.

The secondary analyses will be conducted as the main analysis with a regressive model, testing the difference of a parameter between the two groups. Only the likelihood model will be changed to take into account the type of variable studied: γ distribution for continuous variables such as length of stay and duration of ventilation. Dichotomous variables such as 30-day mortality will be studied with logistic regression.

No statistical procedure for replacing missing values will be used. All variables and subjects will be considered in the descriptive analyses, but, for inference, 20% missing data or more will result in rejection of the variable or individual.

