### Study limitations

The incidence of moderate-to-severe hypoxaemia is the primary study endpoint. A 45% basal incidence of moderate-to-severe hypoxaemia may appear overstated to some experts, but it must be underlined that only severe trauma patients will be included and that a 45% incidence was reported in the last randomized PROMTT trial [13], in the era of damage-control resuscitation [54]. A 15% absolute reduction seems ambitious for a single intervention. However, previous studies using dornase alfa in animal lung injury models and in ventilated patients suffering atelectasis demonstrated striking results [35, 38–41, 55].

Because fluid loading regimens and transfusion strategies are based on local written protocols, they may act as potential confounding variables. However, this will be controlled by the stratification of the randomization at the centre level and adjustment of statistical analyses in cases of differences between groups.

In conclusion, this trial is the first multicentre, randomized controlled, double-blinded study adequately powered to test the hypothesis that aerosolized dornase alfa reduces the incidence of moderate-to-severe hypoxaemia in mechanically ventilated severe trauma patients.

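### The allowance for 25% loss is computed as 200 × 1.25: 250 per arm leaves about 187 evaluable patients, not the 200 that the sample-size section sets out to keep

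*Protocol article*

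**What the plan says.** All the sizing figures are in the Sample size section of the protocol article.

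- Expected effect: "Dornase alfa is expected to reduce the incidence of moderate-to-severe hypoxaemia from 0.45 to 0.30".
- Precision input: "Considering a reasonable standard deviation of 0.03". The section does not say whether this belongs to one proportion, to the difference or to a prior.
- Number needed and target: "200 subjects per arm were estimated to show a difference of more than 0.12". No probability is attached to the target.
- Attrition: "Assuming 25% loss to follow-up, this number was increased to 250 subjects per arm, although these subjects will not be replaced".

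The statistical methods sections (items 20a and 20c) add that missing values will not be imputed, and that individuals with 20% or more missing data are left out of inference. Losses can therefore reduce the number analysed. The Study limitations section describes the trial as a "double-blinded study adequately powered to test the hypothesis".

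**The concern.** An allowance for loss should return the required number once the loss has happened. Here it does not. The loss fraction was applied to the 200 evaluable patients, whereas a loss to follow-up is a fraction of those randomized. Because lost patients are not replaced and missing values are not filled in, the trial has no other way of getting back to 200.

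What is at stake is the evaluable number that the article presents as secured and any operating characteristic quoted for it. A reader who takes the section at face value will believe that the trial can lose a quarter of its patients and still analyse 200 per arm.

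A second, smaller difficulty is that a reader cannot retrace how 200 was obtained, because neither the standard deviation of 0.03 nor the criterion behind 0.12 is defined.

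**Working it through.** **Inputs from the Sample size section:** rates 0.45 and 0.30; 200 evaluable per arm; 25% loss; 250 randomized per arm; no replacement.

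**Inputs not stated, assumed here:** a two-sided 5% test, or success when the posterior Pr(difference > 0) is at least 0.975 under Jeffreys Beta(0.5, 0.5) priors.

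**1. Reproduce the stated figure.** 200 × (1 + 0.25) = 250. The stated number is recovered exactly, so this is almost certainly the sum that was done.

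**2. Apply the stated loss.** 250 × (1 − 0.25) = 187.5 per arm. The shortfall is 12.5 per arm, and 12.5/200 = 6.25%.

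**3. Invert the loss correctly.** Required n = 200/(1 − d).
- d = 0.25: 200/0.75 = 266.7, so 267 per arm and 534 in total (17 more per arm, 34 more overall).
- d = 0.20: 200/0.80 = 250. The stated allocation fits a 20% loss.

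**4. Effect on power for 0.45 versus 0.30.** For the two-sided 5% test,

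power = Φ{[0.15 − 1.96 √(2 × 0.375 × 0.625/n)] / √[(0.2475 + 0.21)/n]}.

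- n = 200: (0.15 − 0.0949)/0.0478 = 1.152, power 0.875.
- n = 187: (0.15 − 0.0981)/0.0495 = 1.049, power 0.853.
- n = 250 (no loss): power 0.936.

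For the posterior criterion, 4,000 simulated trials at each size, with a normal approximation to the posterior, gave 0.879 at 200 and 0.853 at 187. Under either criterion the error costs about 2 to 3 percentage points.

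**5. The standard deviation of 0.03.** Binomial standard deviations at 200 per arm:
- placebo: √(0.45 × 0.55/200) = 0.035;
- dornase alfa: √(0.30 × 0.70/200) = 0.032;
- difference: √(0.4575/200) = 0.048.

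The stated 0.03 is close to the single-arm values and well below that of the difference.

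**6. The difference of more than 0.12.** If the data fall exactly on 45% versus 30% at 200 per arm, a normal approximation gives Φ(0.03/0.0478) = 0.735. One million draws from the Jeffreys posteriors give 0.731. The probability that the difference exceeds 0.12 is thus about 0.73 under a non-informative prior.

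**7. Whether 200 can be reached another way.** Detecting 0.45 versus 0.33 with a one-sided 5% test and 80% power needs 204 per arm. Beta priors with a standard deviation of 0.03 on each rate, combined with 200 patients per arm, give a posterior standard deviation of the difference of about 0.032. Both calculations rest on assumptions that the article does not state, but they land near its figures.

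**The case against.** The strongest reply is that the slip hardly matters. Power at 187 is still about 85% for the planned effect. The primary endpoint is also collected in the first 7 ICU days, so a real loss of 25% may never occur; with a loss of 20% or less, 250 per arm delivers 200 or more. This stands as a limit on the size of the point. It does not rescue the sentence, which assumes 25% and gives a number that covers 20%. The cited Bayesian method and the full protocol are not at hand, but neither could change that sum.

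A reader might go further and infer that the rest of the paragraph is wrong too: that 200 per arm should yield a standard deviation of 0.03 and does not, or that the trial could rarely show a difference above 0.12. The article does not support this. It gives 0.03 as something assumed, not as a result of 200 per arm. It sets no assurance level for 0.12, so any threshold used to call that target missed would be the reader's own. Other readings come close to the stated 200. The case for deleting these figures is therefore not made; the case for defining them is.

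A reader might also contrast the 0.12 target with the analysis aim, which is to show that the frequency "is lower in the dornase alpha group than in the placebo group". Sizing for a margin and then testing for any reduction is not a contradiction, and the posterior threshold may properly sit in an analysis plan that is not shown. Nor does anything tie the interim look at 250 patients to the 0.12 figure, so it does not follow that the monitoring board would be misled on futility.

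**Conclusion.** The inflation is wrong as stated. At the article's own 25% loss, 250 per arm yields about 187 evaluable patients, roughly 6% below the 200 claimed. This part needs no assumption beyond the article's figures.

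The practical effect is small: about 85% power at 187 against 87–88% at 200 for 45% versus 30%. Those percentages rest on success criteria assumed here. They give no ground for saying that the trial is underpowered for its planned effect.

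The standard deviation of 0.03 and the difference of more than 0.12 are undefined in the article, so 200 cannot be verified from it. That is a request for clarification and not a demonstrated error.

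**What to change.** Keep 500 patients and correct the statement in one of two ways:

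- say that 250 per arm allows for a 20% loss to follow-up (200/0.80 = 250); or
- keep the 25% assumption and say that about 187 per arm are expected to be evaluable.

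In either case, give the operating characteristics at the number stated and name the criterion they refer to. Keeping both the 25% loss and the 200 evaluable would need 267 per arm, 34 more patients in all; the small gain in power does not make that necessary.

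As a secondary clarification, add a sentence saying what the standard deviation of 0.03 describes (a single proportion, the difference or a prior) and what probability attaches to showing a difference above 0.12.

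The cost is wording only. No patients are added and the analysis is unchanged; under the second option the quoted evaluable number becomes slightly less favourable.

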### Recruitment {15}

Patients will be recruited in seven French participating hospitals, both university-affiliated and non-university-affiliated and admitting severe trauma patients:
Hôpitaux Universitaires de Strasbourg, Hôpital de Hautepierre (150 severe trauma patients per year)Hôpitaux de Colmar, Hôpital Louis Pasteur (50 severe trauma patients per year)Centre Hospitalo-Universitaire de Reims, Hôpital Maison Blanche (150 severe trauma patients per year)Centre Hospitalier Régional Metz-Thionville, Hôpital de Mercy (50 severe trauma patients per year)Groupe Hospitalier de la Région de Mulhouse et Sud-Alsace, Hôpital du Moenchsberg—Emile Muller (50 severe trauma patients per year)Centre Hospitalier Régional Universitaire de Nancy, Hôpital Central (220 severe trauma patients per year)Assistance Publique—Hôpitaux de Paris, Hôpital Universitaire Pitié Salpêtrière—Charles Foix (500 severe trauma patients per year)

Taken as a whole, more than 3500 patients per year fulfil the inclusion criteria, allowing for an inclusion ratio of one patient included out of seven patients admitted to one of the participating centres.

### Assignment of interventions: allocation

#### Sequence generation {16a}

Randomization will be conducted over a dedicated, password-protected, SSL-encrypted website (CleanWeb; Telemedicine Technologies S.A.S.) to allow immediate and concealed allocation. Allocation will also be stratified by centre and the presence of severe traumatic brain injury (Glasgow Coma Score < 9 on scene).

#### Concealment mechanism {16b}

The experimental study drug and placebo will be provided in identical boxes, allowing double-blind administration. The logistics of the trial fluid distribution to each of the seven participating centres that are anticipated to be recruiting will be coordinated by the pharmacy of the coordinating centre (Hôpitaux Universitaires de Strasbourg).

#### Implementation {16c}

The allocation sequence will be computer-generated (CleanWeb; Telemedicine Technologies S.A.S.). Patients will be enrolled by registered investigators, who will also assign patients to a treatment consisting of either dornase alfa or placebo.

### Assignment of interventions: blinding

#### Who will be blinded {17a}

Trial participants, care providers, outcome assessors and data analysts will remain blinded after assignment to interventions, until the final analysis.

#### Procedure for unblinding if needed {17b}

Unblinding is permissible whenever an adverse event occurs, via immediate request to the poison centre of the study coordinator hospital (Hôpitaux Universitaires de Strasbourg) 24 h per day and 365 days per year. The procedure for revealing a participant’s allocated intervention during the trial includes an explicit mention in the patient record.

### Data collection and management

#### Plans for assessment and collection of outcomes {18a}

Clinical research associates will ensure that patient inclusion, data collection, registry and rapport are in line with the protocol, and that the study is conducted in accordance with the Good Clinical Practice guidelines. Furthermore, clinical research associates will check the following variables: patient initials, date of birth, sex, signed consent form, eligibility criteria, date of randomization, treatment assignment, adverse events and study endpoints. The data monitoring committee is institution-based and independent from potential industrial sponsors.

#### Plans to promote participant retention and complete follow-up {18b}

A dedicated card will be given to any included patient and participation in the TRAUMADORNASE trial will be explicitly mentioned during transfer to another ward or hospital during handovers.

#### Data management {19}

Data will be collected in each centre by clinical data technicians on an electronic case report form (CleanWeb; Telemedicine Technologies S.A.S.) using double password-protected computers. Pre-specified lists, range of values and drop-down menus in the electronic case report form will facilitate data entry and prevent writing errors. Study documents will be de-identified, stored in each recruitment centre and kept for at least 15 years in a locked, secure office, according to French law. All personnel involved in data analysis will be masked. Only the principal investigators and the statisticians will have access to the final data set.

#### Confidentiality {27}

People with direct access to the data will take all necessary precautions to maintain confidentiality. All data collected during the study will be rendered anonymous. Only initials and inclusion number will be registered.

#### Plans for collection, laboratory evaluation and storage of biological specimens for genetic or molecular analysis in this trial/future use {33}

On days 0, 3 and 5, additional blood samples (6 ml on each day) will be drawn into EDTA tubes, centrifuged and stored (− 80 °C) for subsequent analysis of DAMPs (mitochondrial DNA by qPCR; HMGB1, HSP70 and sRAGE by ELISA) at the end of enrolment. In patients included in the Strasbourg centre, whole blood samples will be drawn (days 0, 3 and 5) for extemporaneous quantification of NETs on fresh blood using a flow cytometric assay [45]. The remaining biological specimens will be stored in 0.5-ml aliquots at “Biomax” biobank, Laboratoire d’ImmunoRhumatologie Moléculaire, INSERM UMR_S 1109, [name], France (Pr [name]) for a maximum duration of 15 years (BB-0033-00084, CIM code: I00-I99 / A00-B99 / D50-D89 / M00-M99 / F00-F99 / G00-G99).

### Statistical methods

#### Statistical methods for primary and secondary outcomes {20a}

Statistical analyses will include a descriptive step and an inferential step using fully Bayesian techniques. The estimates will use Markov chains to Monte Carlo integrations (McMC), choosing prior distributions to be nearly conjugated situations. Unless the diagnoses for convergence give clues to the contrary, we will use three Markov chains with separated starting points, a burn-in of 100,000 for each chain and 100,000 more iterations with a thinning of 25 for building a total sample of 12,000 iterations on which the Monte Carlo integrations are used to retrieve characteristics of posterior distributions. The analyses will be carried out using R software (with ad hoc packages) and OpenBUGS. Sensitivity analyses will be systematically conducted, considering three scenarios with different priors: a default non-informative prior (e.g. Jeffreys prior), then an optimist prior and, finally, a pessimist prior.

In the descriptive step, all of the variables collected will be summarized: number and frequency for qualitative variables (ordinal and categorical) and minimum, quantiles (2.5, 25, 50, 75 and 97.5), maximum, mean and standard deviation for quantitative variables (discrete and continuous). For variables gathered over time, these descriptions will be provided globally and at each time. This description will be enriched by inference to extrapolate the observed quantities on the sample. For quantitative variables, we will assume a normal likelihood combined with a normal prior on the mean (mean 0 and variance 100) and γ on the precision (inverse of variance) with parameters 0.0005 and 0.005, and therefore mean 0.1 and variance 20. For binary variables (for which one proportion needs to be estimated), we will assume a binomial likelihood and a β prior on the proportion (Jeffreys prior with parameters 0.5 and 0.5, and thus mean 0.5 and variance 0.125). For categorical variables with more than two categories, we will assume a categorical likelihood together with a Dirichlet prior (Jeffreys prior with all parameters at 0.5).

The aim of this study is to show that the frequency of moderate-to-severe hypoxaemia is lower in the dornase alpha group than in the placebo group. The main variable is then dichotomous “moderate-to-severe hypoxaemia yes/no”, modelled in a logistic mixed regression. We will assume that this variable is Bernoulli distributed with parameter π. The logit of this parameter (linear predictor) is additively written as:
$$ \mathrm{logit}\left({\pi}_i\right)={\alpha}_0+{\alpha}_1I\left({g}_i=1\right)+{\beta}_i, $$

where:
*α*_0_ is a grand mean, with mean 0 normal prior (the variance in this normal is 6, corresponding to a low informative prior)*I*(*g*_*i*_ = 1) is a dummy covariate coded for the group of subject *i* (1 for the dornase alpha group and 0 for the placebo group) — the prior on the parameter of this covariate is the same normal as that for the grand mean*β*_*i*_ is a (random) subject effect, on which is assumed a normal prior with mean 0 and low variance (e.g. 10)

Because the linear predictor is on the logit scale, the probability for moderate-to-severe hypoxaemia will be obtained by monitoring the back-transformation of the logit.

This regression model without covariates except group will be completed for taking into account potential confounding variables. In the model, the entire set of these variables will be added and, secondly, selected using stochastic search variable selection (SSVS) [53]. In such a model, the prior distribution on each parameter is a mixture of two mean 0 normal distributions, one with low variance and the other with high variance: if the posterior weight on this second normal is strongly around 0, then the prior on the parameter is essentially driven by a normal distribution whose mean is centred on 0; this is the clue for a “non-significant” parameter.

The secondary analyses will be conducted as the main analysis with a regressive model, testing the difference of a parameter between the two groups. Only the likelihood model will be changed to take into account the type of variable studied: γ distribution for continuous variables such as length of stay and duration of ventilation. Dichotomous variables such as 30-day mortality will be studied with logistic regression.

No statistical procedure for replacing missing values will be used. All variables and subjects will be considered in the descriptive analyses, but, for inference, 20% missing data or more will result in rejection of the variable or individual.

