### Outcomes {12}

#### Primary endpoint

The primary endpoint will be the incidence of moderate-to-severe hypoxaemia (PaO_2_/FiO_2_ < 200, according to the Berlin definition [5]) in severe trauma patients (ISS > 15) during the first 7 ICU days. The PaO_2_/FiO_2_ ratio will be computed at least once daily (8:00 a.m.) together with the supine chest X-ray and the worst daily PaO_2_/FiO_2_ value will be taken into account to define hypoxaemia severity. In ARDS patients, the severity of hypoxaemia allows for its classification according to the Berlin definition and is strongly associated with mortality, length of recovery and quality of life [6, 7].

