#### Secondary endpoints

The following secondary endpoints will be recorded:
Static lung compliance (ml/cmH_2_O) (measured at least once daily at 8:00 a.m. during the first 7 days)Duration of mechanical ventilation (h) from ICU admission to first extubation success (> 48 h without reintubation)Length of ICU stay (h)Length of stay in the hospital (days)Incidence of multi-organ failure (a SOFA score of 3 or more in at least two organ systems [49]), assessed daily during the first 7 daysIncidence of VAP according to both the American Thoracic Society (ATS) [50] and the Center for Disease Control and Prevention (CDC) [51] definitions, assessed daily during the first 7 daysMortality on day 30

The effects of dornase alfa and normal saline will be assessed according to the plasma concentrations of DAMPs (mitochondrial DNA, HMGB-1, HSP70, sRAGE) and NETs (Strasbourg centre only) divided into quartiles at day 0, day 3 and day 5. It is anticipated that trauma patients with the highest blood concentrations of either DAMPs or NETs will develop the most severe complications (including hypoxaemia and ARDS). The time course of DAMP and NET blood concentrations will also be analysed according to treatment group to unveil a potential quicker decrease in patients randomized in the dornase alfa group.

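### One fixed Normal(0, variance 100) prior for the mean of every quantitative variable is strongly informative for durations in hours and for PaO2/FiO2, and pulls their descriptive posterior summaries well below the data

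*Protocol article*

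**What the plan says.** The statistical methods section {20a} of the protocol article has a descriptive step and an inferential step. The descriptive step lists the usual sample summaries for all collected variables and then adds: "This description will be enriched by inference to extrapolate the observed quantities on the sample". For quantitative variables the model for that added inference is fixed numerically: "we will assume a normal likelihood combined with a normal prior on the mean (mean 0 and variance 100", together with "γ on the precision (inverse of variance) with parameters 0.0005 and 0.005, and therefore mean 0.1 and variance 20". No exception, unit or rescaling is mentioned.

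The secondary endpoints include "Duration of mechanical ventilation (h) from ICU admission to first extubation success" and "Length of ICU stay (h"), so both are in hours. The primary endpoint section defines hypoxaemia by "PaO_2_/FiO_2_ < 200, according to the Berlin definition", so the ratio that is measured daily lies on a scale of hundreds.

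Two other statements limit the reach of the prior. For the comparison of arms, the same section changes the likelihood to a "γ distribution for continuous variables such as length of stay and duration of ventilation". It also promises sensitivity analyses "considering three scenarios with different priors: a default non-informative prior (e.g. Jeffreys prior), then an optimist prior and, finally, a pessimist prior".

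**The concern.** A variance of 100 is an SD of 10, so the prior puts about 95% of its probability on a mean between -19.6 and +19.6 in the recorded unit. The protocol's own figures lie far outside that range. Entry requires expected ventilation of more than 48 h, which is 4.8 prior SDs from zero, and the PaO2/FiO2 threshold of 200 is 20 prior SDs away. The weight of the prior also depends on an arbitrary choice of unit: the same stay counted in days rather than hours would be shrunk far less.

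Binary and categorical variables receive Jeffreys priors in the same paragraph, so the intention was evidently to let the data speak. For large-valued variables the stated normal prior does the opposite. Posterior means and credible intervals for clinically important variables would contradict the sample means printed beside them.

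**Working it through.** **The protocol's own figure.** Gamma with shape 0.0005 and rate 0.005 has mean 0.0005/0.005 = 0.1 and variance 0.0005/0.005² = 20. Both agree with the text, so the precision prior is read correctly and is not the source of the problem.

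**Inputs.** From the protocol: prior N(0, 100) on the mean, Gamma(0.0005, 0.005) on the precision, 250 patients per arm and 500 in total. Assumed, because the protocol gives none: the sample means and SDs, taken over a range from mild to marked. Each n refers to one value per patient (for PaO2/FiO2, one time point). A global summary that pooled all daily values would have a larger nominal n and less pull.

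**Simple form, SD treated as known.** Posterior mean = w × sample mean, with w = 100/(100 + SD²/n). For 240 h, SD 200, n = 250: SD²/n = 160, w = 100/260 = 0.385, posterior mean 92.3 h.

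**Full stated model.** With the precision integrated out, the posterior of the mean μ is proportional to N(μ; 0, 100) × [0.005 + SS(μ)/2]^-(0.0005 + n/2), where SS(μ) = (n-1)SD² + n(sample mean - μ)². It was evaluated on a fine grid. The pull is stronger than in the simple form because a μ far from the data inflates the fitted variance, which in turn gives the prior more weight. Check for the same case: near μ = 62.1 the fitted variance is about 39,840 + 177.9² = 71,488, so w = 100/(100 + 71,488/250) = 0.259 and 0.259 × 240 = 62.2 h, which agrees with the grid result of 62.1 h.

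| Variable, assumed mean (SD) | n = 250: posterior mean (95% interval) | n = 500: posterior mean (95% interval) |
|---|---|---|
| Ventilation 100 h (80) | 78.3 (68.5 to 87.8) | 88.4 (81.6 to 95.2) |
| Ventilation 240 h (200) | 62.1 (42.8 to 81.2) | 113.0 (96.1 to 129.5) |
| ICU stay 360 h (300) | 41.7 (22.0 to 61.3) | 83.1 (63.7 to 102.4) |
| PaO2/FiO2 200 (60) | 168.9 (158.8 to 178.1) | 185.8 (180.2 to 191.2) |
| PaO2/FiO2 250 (100) | 120.9 (98.3 to 142.8) | 199.8 (188.8 to 210.2) |
| Compliance 45 ml/cmH2O (15) | 44.6 (42.7 to 46.5) | 44.8 (43.5 to 46.1) |
| Hospital stay 25 days (20) | 24.6 (22.1 to 27.1) | 24.8 (23.0 to 26.6) |
| Mean arterial pressure 80 mmHg (15) | 79.3 (77.4 to 81.1) | 79.6 (78.3 to 81.0) |

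In the first five rows every interval excludes the sample mean, and the posterior mean lies between 7% (185.8 against 200) and 88% (41.7 against 360) below it. In the last three rows the shift is negligible, because SD/√n is far below 10.

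**Order of the arms, if these summaries were given by arm (n = 250 each).** 240 h (SD 200) and 200 h (SD 180) give 62.1 and 66.5 h: reversed. 240 h (SD 240) and 216 h (SD 216) give 50.7 and 55.4 h: reversed. 240 h and 220 h, both with SD 200, give 62.1 and 60.9 h: not reversed, but a 20 h difference shrinks to 1.2 h.

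**With prior variance 10^6.** The first five rows return the sample mean to within 0.2 of a unit, for example 239.96 h and 359.87 h at n = 250.

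**The case against.** The strongest reply is about scope. The prior sits in the descriptive step, where a single mean is estimated and no comparison of arms is mentioned. Length of stay and ventilation duration are compared between arms under a gamma likelihood in a regression, and the primary endpoint is binary and analysed by logistic regression. PaO2/FiO2 is not itself listed as a quantitative secondary endpoint. All of this stands. A reader might infer that the prior could reverse a treatment comparison of the trial. The documents do not support that: no planned test is said to use this prior, and summaries by arm are not stated for this step. Even with such summaries, reversal is a possibility that arises mainly when the arm with the larger mean also has the larger SD. That is plausible for skewed durations but not assured.

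A second reply is that the error would be visible. Raw means, SDs and quantiles are reported for every quantitative variable, and a non-informative prior is promised among the sensitivity analyses. This makes it unlikely that anyone would be misled without noticing. It does not correct the stated prior, and it would leave two incompatible sets of estimates to explain.

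A third reply is that many variables are unharmed. That is true of compliance, hospital stay in days and mean arterial pressure. It also shows that one fixed variance cannot suit variables on different scales.

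**Conclusion.** The point holds as a scaling error in a stated prior. For variables with a large mean and SD in the recorded unit, chiefly ventilation duration and ICU stay in hours and PaO2/FiO2, the posterior summaries of the descriptive step would be far too low. Over the assumed range the shortfall runs from 7% to 88%, with 95% intervals that exclude the sample mean.

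The exact sizes rest on assumed means and SDs, on the prior being applied to untransformed values in the recorded unit, and on n of 250 or 500. The direction does not depend on the particular values chosen, since pooling both arms reduces the pull without removing it. Severity is minor to moderate: planned posterior summaries are affected, while the primary analysis and the gamma-model comparisons of durations are not.

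**What to change.** Either of two changes repairs the prior.

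- Standardise each quantitative variable with a centre and scale that are fixed in advance and common to both arms, apply N(0, 100) on that scale, and back-transform for reporting. The SD is then about 1, so at n = 250 the weight on the data is 100/(100 + 1/250) = 0.99996.
- Keep the recorded unit and use a variance that is vague in it, such as 10^6.

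For ventilation duration and lengths of stay, use the gamma model already planned for the comparison of arms in the descriptive inference as well, so that the report carries one coherent set of estimates. Add a routine check of each prior against the plausible range of its variable.

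The cost is one sentence in the analysis plan and a scaling line in the code. No data collection, sample size or primary analysis changes.
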